### Eligibility

Potential research participants who meet the eligibility criteria (Table 1) are identified on the stroke unit or in the transient ischemic attack outpatient clinic. All patients undergo a minimum set of diagnostic investigations to assess eligibility, including brain imaging confirming ischemic stroke (computed tomography / magnetic resonance imaging [MRI]), vascular imaging (head and neck), and a minimum of 24 hours of heart rhythm monitoring (telemetry/24-hour Holter). Patients in whom the stroke etiology is determined after study inclusion (for example, if a cause of stroke is identified via CMR imaging) will be excluded from final analysis.

**Table 1 tbl1:** Inclusion and exclusion criteria

Inclusion criteria	Exclusion criteria
• Patient consent or assent can be obtained • Confirmed acute ischemic stroke with evidence on brain CT and/or MRI within 3 months of study enrollment • Ischemic stroke of unknown source with brain imaging suspicious for embolic etiology • Expected survival >12 months • At least 1 additional stroke risk factor (ie, CHA_2_DS_2_VaSc ≥3) • Sinus rhythm on 12-lead ECG, 24 hours of heart rhythm monitoring (telemetry/Holter), and a regular pulse on clinical examination • Above 18 years of age	• Unable to obtain patient consent or assent • History of atrial fibrillation • Atrial fibrillation detected on ECG and/or telemetry/Holter (AF duration of at least 30 seconds required for diagnosis), eGFR <30 mL/min • Indication for pacemaker/implantable cardioverter-defibrillator • Contraindication to undergo cardiac MRI (eg, severe claustrophobia, unable to lie flat for prolonged period, ferromagnetic implant) • Carotid stenosis >50% on duplex ultrasound associated with anterior circulation infarction • Vertebrobasilar stenosis >50% on CT/MR angiography associated with posterior circulation infarction • Single, isolated lacunar stroke with a corresponding lacunar infarct on brain CT/MRI • Specific etiology for cause of stroke (eg, arteritis, dissection, drug abuse)

AF = atrial fibrillation; CT = computed tomography; ECG = electrocardiogram; MR = magnetic resonance; MRI = magnetic resonance imaging.

### Consent

If eligible for recruitment, patients are informed about the study, and a Patient Information Sheet and Informed Consent Form is provided. Capacity to consent is assessed by the patient’s clinical team and should the patient be unable to provide written informed consent, study information is provided to a consultee (next of kin) and assent is subsequently obtained from the patient with the consultee acting as a patient advocate. Patients are recruited via both methods in order to preserve the heterogeneity of the study population.

### Baseline data collection

On enrollment, patient data collected includes patient demographics, preexisting medical history, CHA_2_DS_2_VaSc score, and data from relevant stroke investigations (routine blood panel, carotid Dopplers, computed tomography / MRI brain).

### Noninvasive electrophysiological data

All patients will undergo a 12-lead surface ECG and 24 hours of heart rhythm monitoring using telemetry or 24-hour Holter prior to insertion of an ILR (LINQ; Medtronic, Mounds View, MN). Electrocardiographic metrics to be assessed include mean heart rate, atrial high rate episodes, atrial ectopy burden, PTFV_1_, and PR interval.

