## Objectives

The overall research aim is to produce a substrate-based predictive model using CMR and electrocardiographic parameters that may better identify ESUS patients at risk of developing AF.

The principal research question is to determine if atrial CMR imaging can predict the occurrence of AF in advance of the clinical arrhythmia in patients with confirmed ischemic stroke. The specific hypotheses that will be tested are as follows: (1) left atrial LGE in patients with ESUS is greater in patients with AF than those without AF documented by ILR; and (2) left atrial sphericity in patients with ESUS is greater in those patients with AF than those without AF documented by ILR.

The secondary research question is to determine whether electrocardiographic parameters can predict the occurrence of AF in advance of the clinical arrhythmia in patients with confirmed ischemic stroke. The specific hypotheses that will be tested are as follows: (3) PTFV_1_ in patients with ESUS is greater in those patients with AF than those without AF documented by ILR; and (4) supraventricular ectopy in patients with ESUS is greater in those patients with AF than those without AF documented by ILR.

As described in Data Analysis, below, further analysis will be performed to combine structural and electrical variables into a single score to improve prediction of AF status, which can be employed in future randomized controlled trials.

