#### Implantable loop recorder programming

All patients receive a Reveal LINQ (Medtronic) ILR device as per routine clinical care for detection of AF. Nominals are set to detect increased sensitivity of AF detection threshold, aggressive ectopy rejection, and storage of all AF/atrial tachycardia episodes to maximize AF detection. AF is detected following 2 minutes of ILR monitoring as per the Medtronic AF detection algorithm. Each episode will be reviewed by 2 independent experts prior to study/control group allocation. Daily remote data collection will occur as part of routine clinical care.

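### Hypothesis 4 pools atrial ectopy from telemetry and Holter in an unadjusted two-group test; use a rate and adjust for recorder type

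*Protocol article*

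**What the plan says.** Under Objectives, hypothesis 4 belongs to the secondary research question and states that "supraventricular ectopy in patients with ESUS is greater in those patients with AF than those without AF documented by ILR". No effect size, standard deviation or power is given for it.

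Under Noninvasive electrophysiological data, every patient has "24 hours of heart rhythm monitoring using telemetry or 24-hour Holter prior to insertion of an ILR", and the metrics include "atrial high rate episodes, atrial ectopy burden, PTFV_1_, and PR interval". The section does not say which recorder supplies the ectopy burden or in what unit.

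Under Eligibility, patients are "identified on the stroke unit or in the transient ischemic attack outpatient clinic", and the required work-up includes "a minimum of 24 hours of heart rhythm monitoring (telemetry/24-hour Holter". The same type of monitoring therefore serves as the screen for AF.

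Under Data analysis, groups are compared by t test or, if not normal, by Mann-Whitney U test. Recorder type is not mentioned. Ways of combining the variables into one score are to be explored.

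Under Implantable loop recorder programming, the ILR is set for "increased sensitivity of AF detection threshold, aggressive ectopy rejection, and storage of all AF/atrial tachycardia episodes to maximize AF detection", and "Each episode will be reviewed by 2 independent experts prior to study/control group allocation".

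**The concern.** The baseline recording has two jobs. For excluding AF, telemetry and Holter may both be adequate. For measuring ectopy, the numbers enter a hypothesis test and possibly a prediction score, so a systematic difference between recorders becomes part of the variable. Elsewhere the study holds its measurements to one standard, with a single MRI field strength and a single ILR model. Ectopy is the tested predictor whose stated source is a choice of two recorders.

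Two consequences follow if the recorders read differently:

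- With equal recorder use in the AF and non-AF groups, the offset adds noise and costs power.
- With unequal use, the offset is partly read as a difference between the groups. It can hide a true association or imitate one, depending on which group has more telemetry.

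A smaller issue is length. A minimum of 24 hours permits longer recordings, and an unnormalised count grows with recording time.

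A separate minor issue concerns the outcome. Ectopy rejection on the ILR could make AF harder to detect in patients with much ectopy, so the reference standard might depend slightly on the predictor.

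**Working it through.** **The plan's own figure.** None is given for ectopy. The nearest is the LGE calculation, which fixes the group sizes at 21 and 63. SE = √(9²/21 + 4²/63) = √(3.857 + 0.254) = 2.028; noncentrality 6/2.028 = 2.96; Welch df ≈ 22.7; two-sided 5% power 80.8%, as stated. The same group sizes are used below.

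**Assumed inputs (not in the documents).** Log ectopy has SD 1.5. The true AF minus non-AF difference is 0 or 1.1 on the log scale. Telemetry reads 2 or 4 times lower than Holter, a log offset b of −0.69 or −1.39. The share on telemetry is p_A in the AF group and p_C in the non-AF group.

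**Without any offset.** The standardised difference is 1.1/1.5 = 0.73, and the noncentral t gives 82% power.

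**What pooling does to the comparison.**
- Bias in the group difference = b × (p_A − p_C). For 70% against 40% this is −0.69 × 0.30 = −0.21 or −1.39 × 0.30 = −0.42. Reversing the shares reverses the sign. With equal shares it is zero.
- Within-group variance = 1.5² + b² × p(1 − p). At p = 0.5 this is 2.25 + 0.12 = 2.37 (SD 1.54) or 2.25 + 0.48 = 2.73 (SD 1.65). The standardised difference falls from 0.73 to 0.71 or 0.67.

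**Simulation.** 10,000 trials per setting, pooled Mann-Whitney against a linear model on log ectopy with recorder type as covariate. Each cell gives the 2-fold, then the 4-fold offset.

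| Telemetry share, AF / non-AF | Null rejections, pooled | Null rejections, adjusted | Power, pooled | Power, adjusted |
|---|---|---|---|---|
| 50% / 50% | 5%, 5% | 5%, 5% | 77%, 71% | 81%, 81% |
| 70% / 40% | 8%, 17% | 5%, 5% | 60%, 34% | 79%, 79% |
| 40% / 70% | 8%, 17% | 5%, 5% | 91%, 94% | 79%, 79% |

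Repeat runs move these figures by about a point, so the balanced row is best read as 71–78% pooled against about 82% adjusted. Roughly two points of that gap come from the choice of test: with no offset, the Mann-Whitney test has about 80% power.

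Direction matters. In the 70/40 row nearly all null rejections show ectopy lower in AF, opposite to hypothesis 4. In the 40/70 row nearly all show it higher, which would be false support for the hypothesis.

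**Recording length.** Assume raw counts, SD 1 on the log scale, and 48 or 72 hours instead of 24 in some patients. Null rejections stay at 5% when the shares with longer recordings are equal, rise to 8–12% at 60% against 40%, and to 18–34% at 70% against 30%. A rate per hour removes this effect.

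**ILR ectopy rejection.** Assume a standardised difference of 0.72 (80% power), with AF missed in 10%, 20% or 40% of AF patients whose ectopy is above the AF-group median; those patients count as controls. Power falls to 70%, 57% or 31%. With no true association, rejections are 6%, 7% or 15%, and the bias makes ectopy look lower in AF.

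**The case against.** The strongest reply is that much of this rests on assumptions. No passage says that telemetry and Holter count ectopy differently, that inpatients get one and outpatients the other, or that recorder type is related to AF status. A journal article may also leave the ectopy unit, normalisation and covariates to the full protocol or SAP, so their absence proves little. Hypothesis 4 is secondary, and the sample size rests on LGE and sphericity, which do not use the baseline recorder.

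All of this is fair, and it limits the size of the point. What remains is a stated acquisition choice, two permitted recorders for a quantitative predictor, alongside a stated unadjusted test. A later analysis plan could adjust for recorder type only if the type is captured.

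Two stronger readings do not stand. A reader might infer that the two recorders run for unequal lengths. The section on electrophysiological data gives 24 hours for both; the eligibility wording only permits longer recordings, and length matters only for an unnormalised count. A reader might also infer that the ILR settings contradict their stated aim, since rejecting ectopy cannot by itself increase AF detection. But that aim is attached to a configuration that also raises AF sensitivity and stores all episodes, and the article does not describe how the settings interact. No contradiction is shown. Expert review removes false episodes but cannot recover undetected ones, so under-detection in high-ectopy patients remains possible, and it would work against hypothesis 4.

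**Conclusion.** The point holds as an inexpensive improvement to a secondary analysis. Ectopy may come from two recorders, and the only test named does not account for this. If the recorders differ 2- to 4-fold, balanced use costs roughly 4 to 11 points of power (from about 82% to 71–78%). Unbalanced use biases the result in either direction, with null rejections of about 8–17% at telemetry shares of 70% and 40%, whichever group has the larger share.

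These sizes depend on the assumed offset, spread and shares. If the recorders agree, there is no loss. That recorder use differs by AF status is plausible from the two recruitment settings but not documented, so the documents do not support saying that hypothesis 4 will come out falsely positive or negative. The LGE and sphericity comparisons are unaffected.

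**What to change.** - Define ectopy burden as a rate per hour (or per 24 hours) of analysable recording.
- Record recorder type and analysable duration for each patient. The Baseline data collection section does not list them, so check that they are captured.
- Test hypothesis 4 with recorder type as a stratum or covariate, and enter ectopy in the combined score with the same adjustment.
- Report the Holter-only result as a sensitivity analysis only. With about 21 AF patients expected in all, that subset would be small, and it may over-represent one care setting.
- As a minor addition, report ILR-detected AF by baseline ectopy level, so that readers can judge whether detection varies with ectopy.

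The cost is one degree of freedom, two data items and a few lines of analysis text. If recorder use is unbalanced, adjusted power is about 79% rather than 81% under the assumptions above. Adjustment removes the recorder offset; it does not by itself remove other differences between care settings.

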### Cardiac magnetic resonance imaging

CMR imaging is performed within 3 months of the index stroke and prior to ILR implantation. All imaging is performed on a 1.5 Tesla clinical MRI scanner. Localizer scans are acquired in the 3 standard imaging planes (sagittal, coronal, and transverse), followed by vertical long-axis, horizontal long-axis, and short-axis imaging. Cine imaging of the 4-chamber and 2-chamber views are acquired in end-expiration using a standard balanced steady-state free presession cine technique.

Gadolinium (Gadovist; Bayer HealthCare Pharmaceuticals, Berlin, Germany) is administered at 0.2 mmol/kg at a rate of 0.3 mL/s followed by 30 mL normal saline flush. Following gadolinium, an ECG-triggered, contrast-enhanced magnetic resonance angiogram (CE-MRA) 3D dataset is acquired to delineate the left atrial endocardial border 90 seconds after gadolinium administration, after which a full short-axis stack including the ventricles and atria is acquired.

For LGE imaging, the inversion time is determined from a multiphase inversion time mapping sequence (TI-Scout/Look-locker) performed immediately prior to each LGE scan to ensure adequate nulling of ventricular myocardium. Two separate sequences are used to acquire LGE imaging: a respiratory-navigated sequence and an image-navigated sequence. Respiratory navigator artefacts are a limitation of left atrial imaging that the image-navigated sequence seeks to eliminate.

For image-navigated imaging, an ECG-triggered free-breathing image-navigated dual-echo 3D inversion recovery spoiled gradient echo sequence (iNav LGE) is acquired 15–20 minutes after gadolinium administration according to our previous sequence optimization and routine clinical practice for preablation atrial imaging at our institution.^30^ The 2D image navigators enable data collection throughout respiration, ensuring no data rejection and significantly reducing scan time and, subsequently, motion artefact. Dual echo readout allows for water and fat separation, providing LGE images of both fat suppression and fat distribution.^31^ Coverage includes the left and right atrium. Typical parameters are as follows: TR 7.16 ms, TE 2.38/4.76 ms, flip angle 20°, centric k-space ordering, 1.3 × 1.3 × 4 mm^3^ acquired voxel size with interpolation to 1.3 × 1.3 × 2 mm^3^ during reconstruction, SPIR fat suppression, anterior-posterior phase encoding direction.

For respiratory-navigated imaging, a second LGE sequence is performed 20–25 minutes after gadolinium enhancement. This comprises an ECG-triggered free-breathing diaphragmatic navigated 3D inversion recovery spoiled gradient echo sequence (dNav LGE) that conforms to current clinical standards within our institution for atrial imaging. Coverage includes the left and right atrium. Typical parameters are as follows: TR 4.2 ms, TE 1.8 ms, flip angle 20°, centric k-space ordering, 1.3 × 1.3 × 4 mm^3^ acquired voxel size with interpolation to 1.3 × 1.3 × 2 mm^3^ during image reconstruction, SPIR fat suppression, anterior-posterior phase encoding direction, navigator gating acceptance window of 5 mm in end-expiration.

For all 3 of the 3D sequences (CE-MRA, iNav LGE, dNav LGE) subject-specific trigger delay and acquisition window are identified using the 4-Chamber cine image to identify atrial diastole and reduce cardiac motion artefact. The field of view is identical in both LGEs and the CE-MRA to facilitate registration between the images during postprocessing.

Primary structural metrics collected from CMR imaging include left atrial surface area and volume, visual and quantitative LGE assessment, and sphericity. Secondary anatomical metrics collected include left atrial appendage orifice size and flow.

### Image postprocessing

All CMR scans are postprocessed shortly after acquisition prior to completion of ILR follow-up, patient group assignment, and, where relevant, exclusion of patients owing to the identification of a secondary cause of stroke on CMR imaging (see Eligibility, above). This approach is taken in order to eliminate any potential postprocessing bias after study/control group allocation. Postprocessing is performed using the previously validated open-source Cardiac Electro-Mechanics Research Group App (CEMRG) platform (http://www.cemrg.co.uk).^32^ Imaging is reinterpolated to 1 × 1 × 1 mm^3^. A total of 8–12 semiautomatic axial segmentations of the atrial blood pool are then performed using the CE-MRA image and interpolated to reconstruct a 3D atrial shell. Rigid body registration is then used to align the CE-MRA and dNav LGE image. This is performed by identifying the rotations and translations required to optimize the normalized mutual information as the similarity measure of the 2 images giving rise to a displacement field. This is then used to transform the CE-MRA segmentation and overlay it with the dNav LGE image for review of image alignment. In case of malalignment, segmentation is performed using the dNav image directly.

Next, the pulmonary veins and appendage are removed from the atrial shell. The distal end of each pulmonary vein and the left atrial appendage are manually tagged. Center lines are formed from these points and converge to a central point in the body of the left atrium. Pulmonary vein/appendage clippers are then displayed perpendicular to the entry of the vein/appendage into the body of the left atrium. This is defined by the rate of increase of the cross-section area of the vein/appendage, starting from the distal end of the vein/appendage and toward the atrial body. As the cross-section approaches the atrial body, its area increases substantially; this inflection is used to identify the opening of the chamber. Clippers can be manually adjusted prior to removal of the pulmonary veins/atrial appendage.

The last step prior to analysis is clipping of the mitral valve. In order to provide a clipping plane, the valve is viewed en face and 3 points around the valve are selected at 3, 7, and 10 o’clock to create a best-fit circle that is subsequently used as the orthodrome of a spherical clipper. The clipper is then manually reviewed for accuracy of valve positioning prior to valve removal.

#### Fibrosis assessment

The dNav LGE image is then interrogated and an LGE map generated using a maximum-intensity projection technique whereby a 3 mm external projection and 1 mm internal projection is used by default to adequately capture the full thickness of the atrial wall and to account for minor misalignment between the CE-MRA and LGE imaging. To quantify LGE, a blood pool segmentation is derived using a 3-voxel size erosion of the previously segmented left atrial body. Mean and standard deviation of blood pool signal intensity are automatically calculated and are used as reference values. LGE assessment is then performed using the image intensity ratio method using a range of predefined thresholds.^33^ ROC analysis will be performed to delineate the optimal image intensity ratio for use within the predictive model for identification of study vs control group allocation.

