### Sample size justification

Previous data suggest that ILR monitoring will identify AF in 25% of ESUS patients with a CHA_2_DS_2_VaSc score of 3.^2^ We anticipate that our study population will have a 3:1 ratio of non-AF and AF patients. This ratio has subsequently been validated in the recent LOOP study.^28^

Pilot data analysis was performed using CEMRGapp, using the image intensity ratio to define atrial fibrosis at image intensity ratio >0.97.^29^ This analysis suggested a population mean difference of 6% in left atrial LGE burden between AF and non-AF patients, with standard deviations of 9% and 4% in the AF and non-AF group, respectively (Figure 2). For estimating the sample size required to detect a difference in LGE burden between stroke patients with and without AF, we allow for unequal variances and assume that cases (AF on ILR monitoring) represent 25% of the study population while controls (no AF on ILR monitoring) represent 75% of the study population. Group sample sizes of 21 and 63 would achieve 80.8% power to reject the null hypothesis of equal means when the population mean difference is μ1 − μ2 = 47.0 − 41.0 = 6.0, with standard deviations of 9.0 for group 1 and 4.0 for group 2, and with a significance level (alpha) of 0.05 using a 2-sided 2-sample unequal-variance *t* test.

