## Data analysis

Primary analysis will be performed following 12 months of continuous ILR monitoring with interim and delayed analyses performed at 6 months and 2 and 3 years, respectively. Descriptive statistics will be used to characterize the study population. Structural and electrocardiographic metrics will be summarized. Results will be reported as a comparison between the standard deviation and mean difference. If groups show a normal distribution, *t* test will be performed to assess for a significant difference between groups; otherwise, a Mann-Whitney *U* test will be used. The χ^2^ test will be used for categorical data. Any *P* value <.05 will be considered significant. For qualitative assessment of LGE, patients will be categorized as per our routine clinical practice using combined assessment of both LGE methods as none, mild, moderate, or severe LGE. Survival analysis will be performed using Kaplan-Meier curves with atrial fibrillation as the outcome measure. For qualitative assessment of atrial LGE, our open-source platform, CEMRGApp, will be used to create LGE scores. ROC analysis will be used to determine if there is a quantitative LGE cut-off with adequate specificity and sensitivity to detect atrial fibrillation during follow-up. To combine these variables into a single score, the use of logistic regression, shallow classifiers, atrial computational modeling, or combining variables using summated z-scores will be explored to improve the predictive value for AF.

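### The LGE intensity threshold and then the LGE cut-off are both chosen by ROC against AF status in the same patients, so the predictor's reported accuracy will be optimistic; the threshold for the powered LGE comparison is not named

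*Protocol article*

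**What the plan says.** - **Powered measure.** Under Sample size justification, the pilot analysis was run "using the image intensity ratio to define atrial fibrosis at image intensity ratio >0.97". The LGE power statement is built on that measure: "Group sample sizes of 21 and 63 would achieve 80.8% power to reject the null hypothesis of equal means". It takes mean LGE burdens of 47.0 in AF and 41.0 in non-AF patients, a gap of 6.0, with SDs of 9.0 and 4.0.
- **Threshold choice.** Under Fibrosis assessment, LGE on the dNav image is quantified at a set of candidate ratios whose number and values are not given. Then: "ROC analysis will be performed to delineate the optimal image intensity ratio for use within the predictive model". The same sentence gives the target as telling study from control patients. Under Trial design, those groups are defined by whether AF was detected on the loop recorder.
- **Cut-off choice.** Under Data analysis: "ROC analysis will be used to determine if there is a quantitative LGE cut-off with adequate specificity and sensitivity". The outcome for this cut-off is AF found while patients are followed.
- **Hypothesis 1.** Objectives and Data analysis plan a comparison of LGE between AF and non-AF patients by t test or Mann-Whitney. Neither section says at which intensity ratio LGE is measured for it.
- **AUC precision.** Sample size justification gives 95% interval widths of 0.21 to 0.28 for AUCs of 0.85 to 0.65.

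**The concern.** Two choices about the main imaging predictor are made by looking at the outcome: which intensity ratio counts as fibrosis, and which amount of fibrosis counts as positive. Each choice keeps the option that happens to separate these particular patients best. With about 21 AF cases, some of that separation is chance and will not recur.

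The predictive model is the study's overall aim. Under Trial significance it is expected to form the basis of a randomised trial of anticoagulation by atrial substrate, and to remove the need for loop recorders. Inflated accuracy would pass into that trial's patient selection and sample size.

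The second strand is a gap between the powered measure and the analysis. The 0.97 ratio appears only in the sample size section. A reader of the analysis text cannot tell whether hypothesis 1 will be tested at 0.97 or at the ratio chosen by ROC.

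**Working it through.** **1. The protocol's own figures reproduce.**

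LGE power, Welch t test, n = 21 and 63, difference 6, SDs 9 and 4:
- SE² = 81/21 + 16/63 = 3.857 + 0.254 = 4.111, so SE = 2.028.
- Noncentrality = 6/2.028 = 2.96; Satterthwaite df = 22.7.
- Two-sided power at 0.05 = 80.84% (stated: 80.8%).

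AUC interval width, Hanley-McNeil, for example A = 0.65 with 21 and 63:
- Q₁ = A/(2−A) = 0.4815; Q₂ = 2A²/(1+A) = 0.5121; A² = 0.4225.
- Variance = [0.2275 + 20(0.4815−0.4225) + 62(0.5121−0.4225)]/(21×63) = 0.00526, so SE = 0.0725.
- Width = 2 × 1.96 × 0.0725 = 0.284. At A = 0.85 it is 0.218. With 23 and 69 patients the widths are 0.272 and 0.208 (stated: 0.28 and 0.21).

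Both calculations are for one marker fixed in advance. Neither contains a term for choosing the marker or the cut-off.

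**2. Optimism from choosing the threshold.**

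Simulated studies of 21 and 63 patients with SDs 9 and 4. Each patient has K correlated LGE burdens, one per candidate threshold; the correlation between thresholds i and j is ρ^|i−j|. The best-separating threshold is kept and evaluated in the same patients. K and ρ are assumptions, as the article gives neither. All thresholds are taken to have the same true AUC.

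| K | ρ | Apparent AUC, true 0.50 | Apparent AUC, true 0.65 | Two-sided rejection under no effect, if tested |
|---|---|---|---|---|
| 5 | 0.95 | 0.537 | 0.685 | 9.3% |
| 5 | 0.90 | 0.549 | 0.698 | 10.5% |
| 5 | 0.80 | 0.564 | 0.709 | 13.1% |
| 10 | 0.95 | 0.558 | 0.705 | 12.5% |
| 10 | 0.90 | 0.577 | 0.722 | 16.7% |
| 10 | 0.80 | 0.599 | 0.742 | 22.3% |

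With one fixed threshold, AUC is unbiased and rejection is about 5%. For 5 to 8 thresholds the last column spans about 9–20%. With five thresholds all equally correlated, it is 7.7% (0.95) to 11.6% (0.80). The last column applies only if the selected threshold is used for hypothesis 1.

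**3. Optimism from choosing the cut-off alone.**

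This step needs no assumption about K or ρ. One fixed LGE measure, n = 21 and 63; the cut-off maximising Youden's J = sensitivity + specificity − 1 is picked, and J is compared in the sample and in new patients.

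| True AUC | SDs | Apparent J | J in new patients | Gap |
|---|---|---|---|---|
| 0.70 | 9 and 4 (protocol) | 0.47 | 0.38 | 0.09 |
| 0.70 | equal | 0.38 | 0.26 | 0.12 |
| 0.65 | 9 and 4 (protocol) | 0.41 | 0.31 | 0.10 |

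**4. Both steps together.** At true AUC 0.65 with SDs 9 and 4, choosing the threshold and then the cut-off gives an apparent J of 0.44–0.51 against about 0.32 in new patients.

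**The case against.** - **The selected threshold belongs to the predictive model, not to hypothesis 1.** This stands. A reader might infer that the LGE group comparison is itself biased and no longer matches what was powered. The documents do not support that: Fibrosis assessment confines the ROC-chosen ratio to the model, and nothing says it feeds the test. What remains is that no threshold is named for a comparison powered at 0.97.
- **Scans are processed before allocation.** A reader might infer that choosing the threshold on outcome defeats this safeguard, of which Image postprocessing says "This approach is taken in order to eliminate any potential postprocessing bias after study/control group allocation". It does not. The safeguard protects segmentation, vein and appendage tagging and valve clipping from reader bias, and choosing among burdens already computed changes none of these.
- **The candidate thresholds are predefined.** True, but the choice among them is not.
- **Optimism correction may be in an analysis plan that is not shown.** Agreed, and its absence from a condensed article is not the point. The point is that the article states two outcome-driven selections and leaves the threshold for the powered test open.
- **The model work is exploratory.** Partly. The article says so of combining variables into a score, and asks only whether an adequate cut-off exists. The ROC choice of threshold is stated as a planned step without that label.
- **The 0.97 ratio rests on a small pilot (8 stroke and 8 control patients).** Fair. That is a reason to explore other thresholds, but not to leave the powered comparison without one.

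**Conclusion.** The concern holds in limited form. Followed as written, the plan yields an optimistic AUC, sensitivity, specificity and cut-off for the LGE predictor unless the selection is corrected for.

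- **Cut-off step:** Youden index overstated by about 0.09 at true AUC 0.70 with the protocol's SDs, or 0.12 with equal SDs.
- **Threshold step:** AUC overstated by about 0.03 to 0.10, assuming 5 or 10 thresholds, neighbour correlation 0.80–0.95 and equal true AUC at every threshold. If the thresholds truly differ, part of the apparent gain would be real.
- **AUC interval:** the planned width of 0.21–0.28 describes a prespecified marker and does not cover this shift.
- **Hypothesis 1:** no error is shown, only an unnamed threshold. The rise in its two-sided error from 5% to about 9–20% is conditional on carrying the selected threshold into the test, with 5–8 thresholds and neighbour correlation 0.80–0.95.

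**What to change.** 1. State that hypothesis 1 and the primary LGE ROC use dNav LGE burden at an intensity ratio above 0.97. No selection effect then arises in the test, and the stated 80.8% power still applies.
2. List the other candidate thresholds, and call the ROC-selected threshold and the optimised cut-off exploratory model-building steps.
3. Report those steps with internal validation (bootstrap or nested cross-validation) that repeats both the threshold and the cut-off selection in every resample.
4. Settle this before any analysis by AF group, including the 6-month interim.

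The cost is a few sentences and some programming. The downside is a headline AUC that may be slightly lower than the optimised one.
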